## Abstract

**Background:**

Hypertension is present in more than 50% of patients with type 2 diabetes mellitus. Dietary salt restriction is recommended for the management of high blood pressure. Instructions on dietary salt restriction, provided by a dietitian, have been shown to help patients reduce their salt intake. However, appointments for the dietitians in hospitals are often already fully booked, making it difficult for patients to receive instructions on the same day as the outpatient clinic visit.

**Aim:**

The aim of this trial is to test a new intervention to assess whether guidance on dietary salt restriction provided by physicians during outpatient visits is effective in reducing salt intake in patients with type 2 diabetes mellitus who have an excessive salt intake.

**Methods:**

In this unblinded randomized controlled trial (RCT), a total of 200 patients, male or female, aged between 20 and 90 years, who have type 2 diabetes mellitus and consume excessive salt will be randomly assigned to two groups: an intervention group and a control group. In addition to being given routine treatment, participants in the intervention group will be given individual guidance on restricting their dietary salt intake by a physician upon enrollment. The control group will only be given routine treatment. Participants will be followed up for 24 weeks. The primary outcome will be dietary salt intake, which will be assessed at baseline and at 8, 16, and 24 weeks. The secondary outcomes, including body weight, body mass index, hemoglobin A1c level, blood pressure, blood glucose level, serum lipid profile, and urinary albumin excretion level, will be assessed at baseline and at 8, 16, and 24 weeks.

**Discussion:**

The results of this RCT have the potential to provide a simple and novel clinical approach to reduce salt intake among patients with type 2 diabetes, making regular visits to their physician, in outpatient facilities. This protocol will contribute to the literature because it describes a practical intervention that has not been tested previously, and it may serve as guidance to other researchers interested in testing similar interventions.

**Trial registration:**

University Hospital Medical Information Network (UMIN), UMIN000028809. Registered retrospectively on 24 August 2017. http://www.umin.ac.jp.

## Introduction

According to a recent estimate, about 425 million adults around the world and an estimated 158.8 million adults in the Western Pacific Region are living with diabetes mellitus (DM) [1]. Among the International Diabetes Federation regions, the Western Pacific Region has the highest number of adults living with DM [1, 2]. Moreover, the prevalence of both type 1 and type 2 DM (T2DM) has increased significantly during recent decades [3]. T2DM, being much more common, has been the main driver for the increase in global diabetes prevalence [3]. The results of the National Health and Nutrition Survey in Japan, released in September 2017, reported that there were an estimated 20 million patients with T2DM and prediabetes, of which 10 million patients had T2DM [4].

Hypertension is present in more than 50% of patients with T2DM and contributes significantly to microvascular and macrovascular diseases in T2DM [5]. Moreover, the incidence of cardiovascular disease markedly increases when the two diseases coexist [6]. Thus, intensive treatment of high blood pressure, in addition to hyperglycemia, is important for patients with T2DM.

Epidemiological studies have shown that excessive salt intake is directly related to cardiovascular mortality and to an increase in blood pressure [7]. Many hypertension guidelines recommend salt restriction, based on studies that have demonstrated a decrease in blood pressure with a reduction in salt intake [8, 9]. We have previously reported in a single-arm trial that nutritional instructions on dietary salt restriction by a national registered dietitian provided to patients with T2DM consuming excessive salt may be beneficial in reducing dietary salt intake and home blood pressure [10]. In that study, daily salt intake was significantly reduced by 0.8 g at 2 months and 0.7 g at 6 months after the instruction. Moreover, morning systolic blood pressure was significantly reduced by 2.7 mmHg at 2 months and 5.8 mmHg at 6 months after the instruction. However, dietitians are usually too busy to see patients during their regular clinic visits. Therefore, it would have great clinical significance if this study can demonstrate that shorter and more focused nutritional instructions given to patients by their regular physicians during regular outpatient visits are effective. It might contribute to reducing the financial burden on patients and also the need for patients to have separate consultations with a dietitian.

We plan to investigate a new method of providing advice to patients with T2DM regarding dietary salt restriction for the management of hypertension: nutritional instructions will be given to patients by their regular physicians during regular outpatient visits.

### Aims of study

This randomized controlled trial (RCT) will evaluate whether simplified instructions on how to reduce salt intake, provided by a physician using standardized nutritional guidance materials, will help patients with T2DM consuming excessive salt to reduce their salt intake.

## Methods

### Study design

The study will be an unblinded RCT aimed at testing whether instructions on dietary salt restriction provided by physicians during outpatient visits is effective in reducing salt intake in patients with type T2DM who have an excessive salt intake. A total of 200 patients with T2DM and excessive salt intake (150 from the Hospital of the Kyoto Prefectural University of Medicine, 50 from Kyoto First Red Cross Hospital according to the proportion of outpatients) will be randomly assigned to an intervention group or a control group, using permuted block randomization, with block sizes of ten. Spot morning urine tests will be performed, and the results will be used to estimate their salt intake. The primary outcome will be the change in daily salt intake between baseline and 24 weeks. Each participant will be enrolled for 24 weeks from randomization to the final follow-up assessment and will visit every 8 weeks (Fig. 1).

**Fig. 1 Fig1:**
[figure not shown]
Flow chart of the study

The Standard Protocol Items: Recommendations for Interventional Trials (SPIRIT) checklist is provided as Additional file 1.

### Study setting

The study will be conducted in outpatient clinics at the Hospital of the Kyoto Prefectural University of Medicine and Kyoto First Red Cross Hospital. Participants will be recruited in the outpatient clinics, and all study visits will be conducted in outpatient clinics.

### Recruitment

Participants will be recruited from April 2016 to December 2020.

### Inclusion criteria

Patients will be considered for inclusion in the study if they meet all of the following inclusion criteria: willing and able to give informed consent for participation in this study; male or female, aged between 20 and 90 years old; diagnosed with T2DM (we will apply the Japan Diabetes Society’s “Committee report on classification and diagnostic criteria of diabetes mellitus” for diagnosing diabetes [11]); and salt intake ≥ 6 g per day in patients with hypertension [12], salt intake ≥ 7 g per day in female patients without hypertension, or salt intake ≥ 8 g per day in male patients without hypertension [13]. Daily salt intake will be measured using a spot morning urine sample.

### Exclusion criteria

Patients will be excluded from the study if they have any of the following exclusion criteria: history of or features indicative of an eating disorder; secondary hypertension or malignant hypertension; pregnant, breast-feeding, or planning to become pregnant within the next 6 months; myocardial infarction, cerebrovascular accident, or hospitalization for angina pectoris within the previous 6 months; change in antihypertensive medication and/or antidiabetic medication within the previous month; cardiac failure (grade II, III, or IV according to the New York Heart Association) [14]; atrial fibrillation or severe arrhythmia; advanced renal failure (serum creatinine greater than or equal to 2.0 mg/dL or patient currently on dialysis); life-threatening condition such as a malignant tumor; intercurrent serious infection; significant psychiatric disorder or diagnosed substance abuse; serious neurological disorder, including epilepsy; unable to change their diet (currently in a facility or using home delivery); or recruiting physician considers the patient to be unsuitable for the study for any other reason.

### Study procedures

After confirming that a patient is eligible for the study, written informed consent will be obtained. Upon enrollment, the participants will be randomized to the intervention group or the control group.

#### Control group

During their baseline visit, participants allocated to the control group will be informed of their current salt intake but will not be given instructions by their physician on how to reduce their salt intake. Their physician will give them the same dietary guidance that is routinely given to patients during outpatient visits.

#### Intervention group

During the baseline visit, participants allocated to the intervention group will be informed of their current salt intake and will be given instructions by their physician on how to reduce their salt intake. This will take about 10 min. (For further details, see the Intervention section.) The intervention group will also receive routine education along with educational intervention.

All participants will be asked to attend follow-up visits 8, 16, and 24 weeks after enrollment.

### Allocation

All participants will be randomized to one of the two arms (intervention or control) in equal ratios, using permuted block randomization, with block sizes of ten. An independent researcher will draw lots to assign each participant to a group directly after obtaining the participant’s informed consent. Because of the nature of this study, it will not be possible to blind participants, physicians, or some of the researchers to the treatment allocation.

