### Intervention

During the baseline visit, participants in the intervention group will be informed of their current daily salt intake and the salt intake recommendation levels (as noted in the inclusion criteria) by their regular physician, who will then give them instructions on how to reduce their salt intake, including clear recommendations for food swaps (e.g., change soy sauce to low salt soy sauce). The materials (pamphlets) used and the doctors’ instructions will be standardized. Instructions on reducing salt intake will be given using pamphlets describing “Twelve tips on reducing salt intake” (listed below); “Specific examples of amount of seasoning equivalent to 1 g of salt”; and “Concrete example of estimated amount of salt contained in food (menu for eating out, dried fish, paste products, processed food, instant food, pickles, *tsukudani*, and delicacies)”. The intervention will take about 10 min. Participants will also be informed of their current daily salt intake at the 8-week and 16-week study visits.

The 12 tips on reducing salt intake are:
Get used to more mild flavors.Limit your intake of pickles and soup.Use salt sparingly.Dip, do not douse, food in salty sauces such as soy sauce.Flavor food with sour-tasting ingredients.Use spices liberally.Use natural aromatic seasonings such as herbs and perilla.Fragrant smells are your friend (grill, roast, toast, etc.).Use flavorful oils such as sesame oil, olive oil, and herbal oil.Limit your intake of snacks that you eat with alcohol.Limit your intake of fish cakes and processed foods.Do not overeat.

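### One disclosed block size of ten in an open trial lets late-block allocations be deduced by staff who have discretion over entry

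*Protocol article*

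**What the plan says.** All of these statements are in the Protocol article.

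- **Block size.** Study design and Allocation both give permuted blocks of a single size: "using permuted block randomization, with block sizes of ten". The ratio is 1:1.
- **Who allocates, and when.** "An independent researcher will draw lots to assign each participant to a group directly after obtaining the participant’s informed consent" (Allocation).
- **Blinding.** "it will not be possible to blind participants, physicians, or some of the researchers to the treatment allocation" (Allocation).
- **Who delivers the guidance.** Intervention-group patients are told their salt intake "by their regular physician, who will then give them instructions on how to reduce their salt intake" (Intervention). Control patients get no such instructions from their physician (Control group).
- **Discretion over entry.** The last exclusion criterion applies if the "recruiting physician considers the patient to be unsuitable for the study for any other reason" (Exclusion criteria).
- **Sites and timing.** The 200 patients are to come as "150 from the Hospital of the Kyoto Prefectural University of Medicine, 50 from Kyoto First Red Cross Hospital according to the proportion of outpatients" (Study design). Trial status describes the trial as ongoing, so the block size was published while patients were still being entered.

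**The concern.** Permuted blocks keep the arms balanced by making later allocations depend on earlier ones. With a block size that is fixed and known, anyone who has followed a block can tell when one arm is used up. Here the people who could follow it are not blinded, and at least some of them decide whom to approach or exclude.

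If a physician expects guidance to be next and brings forward a motivated patient, or holds one back when control is due, the arms differ in motivation before treatment starts. Salt intake depends on dietary behaviour, so such a difference would feed directly into the primary comparison. Measuring the outcome in urine protects against biased assessment. It does not protect against differences in who was entered, and the analysis cannot reliably remove that bias afterwards.

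**Working it through.** The plan gives no figure on predictability, so there is none to reproduce.

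**Inputs from the article:** block size 10, so m = 5 per arm; total 200, so 20 blocks; two hospitals with 150 and 50 patients.

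**1. Worst case: the observer sees every allocation and knows where each block starts.**
- Allocations known with certainty per block: 2m/(m+1) = 10/6 = 1.67, which is 16.7%. Over 20 blocks this is 20 × 1.67 ≈ 33 of 200.
- Correct guesses per block, always guessing the arm with more places left: m + (4^m / C(2m, m) − 1)/2 = 5 + (1024/252 − 1)/2 = 6.53 of 10, or 65.3%, against 50% by chance.
- Simulation agrees: 1.667 certain per block and 65.3% correct.

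**2. Partial view.** The article does not say how many physicians recruit or what each one sees, so the share seen is an assumption. In this simulation the observer sees each allocation with the stated probability and still knows the block boundaries.

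| Share of allocations seen | Certain | Guessed correctly |
|---|---|---|
| 100% | 16.7% | 65.3% |
| 75% | 4.0% | 59.8% |
| 50% | 0.5% | 56.7% |
| 25% | about 0.01% | 54.0% |
| 10% | 0% | 52.2% |

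The 75% and 25% rows correspond to someone who sees everything at the larger or the smaller hospital when one list serves both (150/200 and 50/200). If each hospital has its own list, someone who sees everything at that hospital is back in the first row.

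**3. Effect of varying the block size.** Simulation of 200 allocations with sizes drawn at random and boundaries unknown. The observer uses only the running difference between arms and is certain when it reaches half the largest size. Someone who also reasons about possible boundaries could do somewhat better.

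| Block sizes | Certain | Guessed correctly |
|---|---|---|
| Fixed 10 | 16.7% | 65.3% |
| 4, 6, 8 | 0.15% | 68.0% |
| 6, 8, 10 | 0.03% | 66.4% |
| 8, 10, 12 | about 0.01% | about 65% |

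Varying the size removes nearly all certain prediction. It does not reduce best-guess success, and sets that include small blocks raise it.

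**The case against.** **The observer is assumed.** The guidance comes from the regular physician, while the discretion belongs to the recruiting physician. The article does not say that these are always the same person, or that anyone follows other physicians' allocations. This stands, and it makes 16.7% a worst case rather than an expected value.

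**There are safeguards.** The lot is drawn by an independent researcher, after eligibility is confirmed and consent given. Table 1 even places screening and consent eight weeks before allocation, although the Allocation section has the lot drawn directly after consent. Ten is also a fairly large block: fixed blocks of four would give 70.8% correct guesses. These points reduce the risk but do not remove it. An independent draw conceals the next lot, yet past allocations remain visible, and the decision to approach or exclude a patient comes before consent.

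**Stronger readings that the document does not support.** A reader might infer that recruiting physicians did foresee allocations and select patients. Nothing in the article shows this.

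A reader might also count the absence of stated stratification by hospital as an error. The article is silent on whether the list is common or separate, and a condensed article may leave that to the full protocol. The consequence is small in any case. Under one common list with sites entering in random order, a hypergeometric calculation (200 patients, 100 per arm, 50 at the smaller hospital) gives a 25% chance that the arms there differ by 8 or more. A 21:29 split, with 100 per arm overall, changes the site mix by 8 percentage points. Even an assumed 1 g/day difference between hospitals would then move the unadjusted contrast by 0.08 × 1 = 0.08 g, against a planned 1 g effect. That is chance imbalance, which a hospital term can handle.

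The two worries also cannot both apply in full. Separate lists would form 15 and 5 complete blocks, balanced exactly within each hospital, but would restore full predictability there. A common list weakens prediction for staff who see only one hospital.

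**Conclusion.** The point holds for the fixed block size. The article commits to one block size and discloses it during recruitment, in an open trial where physicians see their own patients' allocations and entry is partly discretionary. Late-block allocations can therefore be deduced from earlier ones.

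The size ranges from 16.7% of allocations certain (about 33 of 200), for an observer of every allocation who knows the boundaries, down to practically none for an observer of a quarter of them. Where the trial lies in that range depends on recruitment arrangements that the article does not describe. Nor does it give any basis for expressing the possible bias in grams of salt per day. It is a recognised design weakness with a cheap remedy, of minor to moderate weight, and not a demonstrated failure of concealment.

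**What to change.** For all remaining allocations, replace the current scheme with a computer-generated list whose block sizes vary at random, are not small (for example 8, 10 and 12) and are not disclosed to recruiting staff. The independent researcher should hold the list. State whether it is common to both hospitals or separate, and include hospital as a covariate in the primary mixed model.

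Avoid sets such as 4, 6 and 8, for the reason shown in the second table.

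The cost is one new list, a short amendment and two allocation procedures to report. The change does nothing for patients already allocated, and best-guess prediction stays at about 65% for someone who sees the whole sequence.

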### Intervention

During the baseline visit, participants in the intervention group will be informed of their current daily salt intake and the salt intake recommendation levels (as noted in the inclusion criteria) by their regular physician, who will then give them instructions on how to reduce their salt intake, including clear recommendations for food swaps (e.g., change soy sauce to low salt soy sauce). The materials (pamphlets) used and the doctors’ instructions will be standardized. Instructions on reducing salt intake will be given using pamphlets describing “Twelve tips on reducing salt intake” (listed below); “Specific examples of amount of seasoning equivalent to 1 g of salt”; and “Concrete example of estimated amount of salt contained in food (menu for eating out, dried fish, paste products, processed food, instant food, pickles, *tsukudani*, and delicacies)”. The intervention will take about 10 min. Participants will also be informed of their current daily salt intake at the 8-week and 16-week study visits.

The 12 tips on reducing salt intake are:
Get used to more mild flavors.Limit your intake of pickles and soup.Use salt sparingly.Dip, do not douse, food in salty sauces such as soy sauce.Flavor food with sour-tasting ingredients.Use spices liberally.Use natural aromatic seasonings such as herbs and perilla.Fragrant smells are your friend (grill, roast, toast, etc.).Use flavorful oils such as sesame oil, olive oil, and herbal oil.Limit your intake of snacks that you eat with alcohol.Limit your intake of fish cakes and processed foods.Do not overeat.

### Measurements and outcomes

All outcome measures will be assessed at baseline and at the 2-month, 4-month, and 6-month follow-up visits (Table 1). Data and safety monitoring will be conducted at all sites periodically during the study.

**Table 1 Tab1:** Overview of enrollment and assessment schedule

	Study period				
	Enrollment	Allocation	Post-allocation		
Timepoint	–8 weeks	0	8 weeks	16 weeks	24 weeks
Enrollment:					
Eligibility screen	X				
Informed consent	X				
Allocation		X			
Interventions:					
Guidance on dietary salt restriction		X			
Informing of salt intake:					
Intervention groups		X	X	X	X
Control groups		X			
Assessments: (both groups)					
Demographics	X				
Dietary salt intake	X	X	X	X	
Medication review	X	X	X	X	
Body weight	X	X	X	X	
Blood pressure	X	X	X	X	
Hemoglobin A1c	X	X	X	X	
Fasting blood glucose	X	X	X	X	
Serum lipid profile	X	X	X	X	
Renal function	X	X	X	X	
Liver function	X	X	X	X	
Urinary sodium/potassium ratio	X	X	X	X	
Urinary albumin excretion	X	X	X	X	

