#### Primary outcome

The primary outcome will be dietary salt intake and will be assessed at baseline and at 8, 16, and 24 weeks. For feasibility, daily salt intake will be measured using a spot morning urine sample and will be calculated using the following equation:

Daily salt intake (g/day) = 0.0585 × 21.98 × {urinary sodium (mEq/L)/urinary creatinine (mg/dL) × (14.89 × body weight (kg) + 16.14 × height (cm) – 2.04 × age (years) – 2244.45)}^0.392^ [15]. Spot morning urine samples will be collected using an immunoturbidimetric assay (Autokit Micro Albumin, Wako, Osaka, Japan).

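### Table 1 marks no outcome assessment at 24 weeks, contradicting the text, which sets the primary outcome at 24 weeks

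*Protocol article*

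**What the plan says.** The text gives the same timing wherever it mentions it. Study design states: "The primary outcome will be the change in daily salt intake between baseline and 24 weeks". It counts the 24 weeks from randomization, with a visit every 8 weeks. The Primary outcome section states: "The primary outcome will be dietary salt intake and will be assessed at baseline and at 8, 16, and 24 weeks". The Abstract gives the same times. The Intervention group section calls all participants back at 8, 16 and 24 weeks. The opening of Measurements and outcomes says the same in months and points to the table: "All outcome measures will be assessed at baseline and at the 2-month, 4-month, and 6-month follow-up visits (Table 1".

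Table 1 has five time columns: −8, 0, 8, 16 and 24 weeks. Its primary-outcome row reads "Dietary salt intake X X X X", with the marks under the first four columns and the last cell empty. The row for telling the intervention group its salt intake reads "Intervention groups X X X X", with the first cell empty and the marks under 0, 8, 16 and 24 weeks.

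Three other statements bear on the table:

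- **Allocation.** "An independent researcher will draw lots to assign each participant to a group directly after obtaining" the participant's consent. Table 1 puts consent at −8 weeks and allocation at 0.
- **Intervention.** After baseline, "Participants will also be informed of their current daily salt intake at the 8-week and 16-week study visits". Week 24 is not named.
- **Inclusion criteria.** Eligibility depends on a salt intake estimated from a spot morning urine sample.

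**The concern.** The table cited as the assessment schedule has no measurement at the primary time point. A coordinator who used it as a checklist would take the last urine sample at 16 weeks, and a missed 24-week sample cannot be recovered afterwards. The Trial status section says the trial is ongoing.

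The table also raises the question of which sample is the baseline. Salt intake is marked twice before or at allocation, and no sentence says which value enters the change score. Patients are selected for high estimated intake, so the choice affects the size of the change seen within each arm.

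**Working it through.** No power or sample-size arithmetic applies. The check is a cell-by-cell comparison of Table 1 with the text.

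**1. Table 1 against the text**

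| Item | Times in Table 1 (weeks) | Times in the text (weeks) |
|---|---|---|
| Dietary salt intake | −8, 0, 8, 16 | baseline, 8, 16, 24 |
| Ten other repeated assessments, from medication review to urinary albumin excretion | −8, 0, 8, 16 | baseline, 8, 16, 24 for all outcome measures |
| Informing the intervention group of its intake | 0, 8, 16, 24 | baseline, 8, 16 |
| Consent, then allocation | −8, then 0 | allocation directly after consent |

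Repeated assessments marked at 24 weeks: 0 of 1 + 10 = 11. The last marked measurement falls 24 − 16 = 8 weeks before the primary time point. The only mark in the 24-week column is feedback to the intervention group, which is not a measurement.

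**2. Could this be a fault in reading the PDF?** Each row has five cells. Rows that begin at week 0 (allocation, guidance, informing) keep their empty first cell, and the 11 assessment rows keep an empty last cell. A reading fault would have had to shift one block and leave its neighbours aligned. That is unlikely but not excluded, so the typeset table should be checked.

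**3. Is there one obvious repair?** The assessment rows carry four marks and the text names four times. Moving the block one column to the right gives 0, 8, 16 and 24, which agrees with the text. That move removes the salt-intake mark at −8 weeks, where the table also places the eligibility screen. The separate eligibility mark could cover the screening sample, but the article does not say so. The authors have to state it.

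**4. Which sample is the baseline?** The Control group, Intervention group and Intervention sections describe the baseline visit as the one at which allocated participants are told their intake and, in the intervention arm, receive guidance. Table 1 places those events at week 0, so the baseline visit is week 0. What remains open is which urine sample supplies the baseline value, since salt intake is marked at both −8 and 0.

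**5. Two possible starting points.** The Intervention group section counts visits from enrollment, and Table 1 heads its −8-week column Enrollment. Counted from there, the visits fall at −8 + 8 = 0, −8 + 16 = 8 and −8 + 24 = 16 weeks. Together with −8 itself, these are exactly the four columns marked. Study design counts 24 weeks from randomization, and Study procedures randomizes upon enrollment, so in the text the two starting points coincide. Only the 8-week gap in the table separates them.

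**The case against.** The strongest reply is that this is a displaced block of marks in a condensed journal article. The Abstract, Study design, the Intervention group section, the sentence introducing Table 1 and the Primary outcome section all provide for a 24-week visit or assessment, and none contradicts it. Nothing shows that the two hospitals work from this printed table. This largely stands. It limits the error to the table but does not remove it, because the article cites that table as its schedule and the empty cell is at the primary time point.

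Four stronger readings are tempting, and the documents do not support them:

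- **The primary outcome cannot be obtained.** A reader might infer this from the table alone. It fails because the text fixes the 24-week measurement repeatedly.
- **The final measurement is really 16 weeks after guidance.** Counting from the −8-week column suggests this, but Study design counts the 24 weeks from randomization.
- **Regression to the mean biases the result.** If the sample that selected high-intake patients were also the baseline, both arms would be expected to fall. Under randomization the expected fall is the same in each arm and cancels in the between-group contrast. Only within-arm changes would be affected.
- **The 24-week feedback entry proves that a sample is taken then.** The feedback could report the 16-week result, so the entry settles nothing.

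**Conclusion.** Table 1 is wrong as printed. All 11 repeated assessments, including the primary outcome, lack a mark at 24 weeks, and the text requires one. The error is an internal inconsistency confined to the schedule table, most plausibly typographical. It should still be corrected, because it concerns the primary time point and the loss would be irreversible for any participant whose site followed the table.

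The baseline question is partial: the visit is identifiable as week 0, but the sample is not named. The consent-to-allocation conflict and the 24-week feedback entry are real and secondary.

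This conclusion assumes that the column positions were read correctly from the PDF. How many sites use the printed table is unknown, so no count of affected participants can be given.

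**What to change.** 1. In Table 1, mark dietary salt intake and the ten other repeated assessments at 24 weeks.
2. Add one sentence stating that the week-0 sample, taken before guidance, is the baseline for the primary outcome, and that the −8-week sample, if taken, serves eligibility only.
3. Reconcile the timing of consent and allocation in Table 1 with Study procedures and Allocation, and state the event from which weeks are counted.
4. Reconcile the 24-week feedback entry in Table 1 with the Intervention section.
5. Confirm that the working schedule at both hospitals carries the 24-week sample.

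The cost is corrections to one table, a sentence of definition and a check with two sites. No new visit is needed, because the text already provides for one at 24 weeks, and the sample size does not change.
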